### Withdrawal Criteria

Withdrawal criteria are as follows: (1) patient withdraws consent; (2) newly find misdiagnosis at baseline; (3) patients are lost to follow-up; (4) investigator's decision to withdraw the subject.

For any subject withdrawal, the reasons for withdrawal will be documented.

### Intervention

#### The Isolation and Culture of hUC–MSCs

The hUC–MSCs are isolated from Wharton's jelly (WJ) of the umbilical cord (UC). The parents who donated signed the informed consent. After aseptically collecting the samples of UC, scrape the WJ away from the blood vessels and inner epithelium of the subamnion. Then WJ is mechanically cut into small pieces of no more than a few millimeters in length. The pieces were transferred to culture flasks, which contained Dulbecco's Modified Eagle Medium-F12 (DMEM-F12) and 10% FBS (Fetal Bovine Serum), then it was incubated in a humidified atmosphere containing 5% CO2 at 37°C. The cells migrate from the explant to medium margins.

#### The Transportation and Storage of hUC–MSCs

The hUC–MSCs will be immersed in liquid nitrogen, carried in a portable liquid nitrogen container, and will be transported to the research centers by a cold chain logistic company. There will be a real-time recording of the temperature inside the liquid nitrogen container. The hUC–MSCs will be stored in liquid nitrogen until resuscitation and infusion.

#### Resuscitation of hUC–MSCs

A thermostat water bath will be preheated to 37°C. A metal clip will be precooled in liquid nitrogen and then the freezing bags of MSCs will be extracted. The freezing bags will be quickly dropped into the water bath and swayed back and forth gently until totally melting (time duration: 2 min).

#### Inspections of hUC–MSCs

The subjects can be infused hUC–MSCs only after the sample tests meets the following requirements:

(1) Total cell amount 5 × 10^7^ ± 10% per package; cell viability over 85%;(2) Bacterial endotoxin test negative; gram-staining negative.

#### Transfusion of hUC–MSCs

Subjects in the intervention groups will receive four hUC–MSC infusions every 3 months besides the primary drugs. The dosages are 1, 2, or 5 × 10^6^ MSCs per kg of body weight. The hUC–MSCs will be infused *via* the subjects' peripheral veins. The drip rate is 30 drops per min in the first 15 min of infusion and 45 drops per min in the next 15 min. If there are no adverse effects, the drip rate can be gradually increased, but never exceed 70 drops per min. The time of infusion should last no more than 1 h. After the infusion of MSCs, subjects will be infused with 500 ml normal saline.

Subjects in the control group will receive four stem cell base solution infusions (the same packaging bag as hUC–MSCs) every 3 months besides the primary drugs.

#### Participant Safety Protection Measures

(1) Subjects will be admitted to the hospital when receiving the infusion;(2) Intravenous infusion of dexamethasone of 5 mg will be given to subjects 15 min before the infusion of hUC–MSCs;(3) Subjects will have electrocardiogram monitoring during the whole process of infusion;(4) Subjects will be discharged after a 2–4 days observation period after the infusion.

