### Study Design

This is a prospective study for an open-labeled, prospective, multicenter, randomized, placebo-controlled clinical trial. The estimated study period is from March 2019 to March 2025. The NMOSD patients in the remission phase will be randomized into two groups: the treatment group (hUC–MSC infusion plus regular treatment) and the controlled group (stem cell base solution infusion plus regular treatment). All the patients will be treated and followed up for 2 years.

The whole clinical trial includes three consecutive stages.

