### Group Allocation, Randomization, and Blinding

The first phase of the trial is an open-label, dose-escalation study that will be performed in a leading center, the Shanghai Ren Ji Hospital. For stages 2 and 3, allocation sequences were generated by an independent statistician by permuted blocks randomization method (block sizes of four or eight). The conceal of allocation sequences were performed by using an integrated web response system (IWRS). The research physician will enroll participants and then assign participants to interventions according to allocation results from IWRS. In stage 2, there are four arms, which are the low dose group (1 × 10^6^ MSC / kg·weight), the medium dose group (2 × 10^6^ MSC / kg·weight), the high dose group (5 × 10^6^ MSC / kg·weight), and the control group (stem cell base solution). Patients will be assigned randomly in a 1:1:1:1 ratio to hUC–MSC groups and control group, respectively. In stage 3, there are two treatment arms. Patients will be assigned randomly in a 1:1 ratio to the hUC–MSC group and control group, respectively. To avoid ethical problems, we designed an add-on trial. Patients in the placebo-controlled group will receive a placebo while they already receive an established regular treatment (azathioprine or mycophenolate mofetil). Therefore, the allocation ratio of 1:1 was based on optimal statistical power and add-on trial design. In stages 2 and 3, all the participants, investigators, and statistician are blinded to group allocation until the end of the study and data analysis. Only pharmacists who are in charge of preparing study drugs are not blinded. Double-blinding will be performed *via* a centralized randomization system. Subjects who leave the study after random allocation will not be replaced.

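### Dexamethasone before and saline after infusion are written for hUC–MSC only; followed literally in blinded stages 2 and 3, they would mark the active arm

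*Protocol article*

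**What the plan says.** The Intervention part of the Protocol article describes the infusion in two adjacent sections.

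- **Participant Safety Protection Measures.** Item 2 reads "Intravenous infusion of dexamethasone of 5 mg will be given to subjects 15 min before the infusion of hUC–MSCs". The other three items (hospital admission, cardiac monitoring, discharge after 2–4 days) name no product. Item 3, for example, reads "Subjects will have electrocardiogram monitoring during the whole process of infusion".
- **Transfusion of hUC–MSCs.** The paragraph on the intervention groups gives dose, route, drip rate and time limit, and closes with "After the infusion of MSCs, subjects will be infused with 500 ml normal saline". A separate paragraph deals with controls: "Subjects in the control group will receive four stem cell base solution infusions (the same packaging bag as hUC–MSCs) every 3 months", in addition to their primary drugs. It mentions neither steroid nor saline.

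Study Design defines the contrast as hUC–MSC or base solution, each with regular treatment, and names no premedication in either arm.

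For stages 2 and 3, Group Allocation, Randomization, and Blinding states that "all the participants, investigators, and statistician are blinded to group allocation until the end of the study and data analysis". It adds: "Only pharmacists who are in charge of preparing study drugs are not blinded".

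**The concern.** Using the same bag for cells and base solution is a genuine masking step. It hides the allocation only if everything around the bag is also the same. A steroid given shortly before one product, and a large saline infusion given after it, are both visible at the bedside. If only active patients receive them, the bag no longer conceals the arm.

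What is at stake is the credibility of the blind in the stages meant to choose the dose and show effectiveness. The primary endpoint is a relapse recognised from new or worsening symptoms after other explanations are ruled out. EDSS, OSIS and the Hauser index are rated in clinic, and SF-36 is answered by the patient. All of these can shift when the patient or the rater knows the treatment.

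**Working it through.** No figure in the plan is in question, so the check is a comparison of text.

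**1. Do the two steps apply to the blinded stages?** Neither is limited to open-label stage 1. Where the article wants a stage 1 measure it says so, as with the telephone interviews under Follow-Up. The Transfusion section also describes a control group, which exists only in stages 2 and 3.

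**2. What is written for each arm?**

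| Step | hUC–MSC arms | Base-solution control |
|---|---|---|
| Four infusions, 3 months apart | stated | stated |
| Packaging bag | stated | stated to be the same |
| Dexamethasone 5 mg, 15 min before | stated | nothing stated |
| 500 ml saline after | stated | nothing stated |
| Route, drip rate, 1 h limit | stated | nothing stated |
| Admission, cardiac monitoring, 2–4 days' observation | stated for subjects, no product named | same wording applies |

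**3. The difference under the literal reading.** At each infusion visit an active patient has three intravenous administrations (dexamethasone, cells, saline) and a control has one. Table 1 places infusions at V1 to V4, that is months 0, 3, 6 and 9. Over the course:

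- dexamethasone: 4 × 5 mg = 20 mg, against none specified for controls;
- saline: 4 × 500 ml = 2000 ml, against none specified for controls.

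These are differences in exposure, not estimates of bias.

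**4. Against the blinding statement.** Whoever gives dexamethasone 15 minutes ahead of cells, but not ahead of base solution, must know what the bag holds. The blinding section allows that knowledge only to the pharmacists preparing study drugs. Without a dummy, blinded staff cannot follow the literal rule.

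**5. Which assessments are exposed?** Table 1 schedules EDSS, OSIS, Hauser index and SF-36 at V2 to V9, eight visits after baseline. All eight follow the first infusion at V1, and three of them (V2, V3, V4) are also infusion visits. Relapse is followed over the same 24 months.

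**6. What is not exposed?** The three active doses in stage 2 receive the same steps under either reading, so the comparison among doses is unaffected. Only comparisons with control are at issue.

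**The case against.** The strongest reply is that the article never says controls go without these steps, and that a common procedure is the natural reading. Three things support it.

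- The drip rate and duration ("never exceed 70 drops per min. The time of infusion should last no more than 1 h") and the peripheral-vein route are also given only for hUC–MSCs. Read literally throughout, controls would have no route, rate or duration, which is implausible for an infusion from a matching bag.
- Discontinuation of Study Intervention speaks of intolerance to MSC infusion where study infusion in general seems meant, so the authors do use the term as shorthand.
- This is a condensed article, and details of placebo logistics commonly sit in the full protocol. A dummy supplied by the unblinded pharmacist is not excluded.

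Most of this stands, and it rules out the inference that controls actually receive no steroid or saline. It does not remove the point. The article does more than leave a detail out: it states a product-specific rule, in a list whose other items name no product, and that rule as worded does not fit its own blinding section. Table 1 shows that the authors can name both products when they mean both, since its treatment row covers hUC–MSC or placebo.

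A reader might also infer two stronger harms that the document does not support:

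- **A biased safety comparison.** Infusion reactions are under intensive monitoring, and a steroid given to one arm could suppress them there. However, Statistical Analysis draws safety indicators only from those given at least one hUC–MSC infusion. No comparison of infusion reactions with control is specified, so this harm arises only if one is made.
- **A relapse effect produced by the steroid.** Four 5 mg doses over the first nine months of a 24-month follow-up probably confound relapse little. Nothing in the document allows the effect to be computed.

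**Conclusion.** The point holds as a conflict between the written infusion procedure and the stated blinding, and it should be fixed. If sites follow the text, active patients are identifiable at up to four visits, beginning before any post-baseline assessment. If sites already treat all arms alike, the text misdescribes the trial. Either way the wording needs correcting.

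The weight of the point rests on possible unmasking. That depends on the literal reading being followed and no dummy being used. The effect on ratings would further depend on whether those who judge relapse and score disability see or learn of the infusion procedure, and on what patients have been told about it. The document settles none of this, so no size of bias can be given. Confidence is moderate.

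**What to change.** Change two phrases. In item 2 of Participant Safety Protection Measures, have dexamethasone given before each study infusion (hUC–MSC or base solution). In Transfusion of hUC–MSCs, have the saline given after each study infusion. Add one sentence stating that route, drip rate, the 1 h limit, cardiac monitoring and the observation period are identical in all stage 2 and 3 arms.

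If controls do not already receive these steps, each would get up to four 5 mg doses of dexamethasone and four 500 ml saline infusions. If they already do, the cost is wording only. No extra patients, visits or analyses are needed.

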### Group Allocation, Randomization, and Blinding

The first phase of the trial is an open-label, dose-escalation study that will be performed in a leading center, the Shanghai Ren Ji Hospital. For stages 2 and 3, allocation sequences were generated by an independent statistician by permuted blocks randomization method (block sizes of four or eight). The conceal of allocation sequences were performed by using an integrated web response system (IWRS). The research physician will enroll participants and then assign participants to interventions according to allocation results from IWRS. In stage 2, there are four arms, which are the low dose group (1 × 10^6^ MSC / kg·weight), the medium dose group (2 × 10^6^ MSC / kg·weight), the high dose group (5 × 10^6^ MSC / kg·weight), and the control group (stem cell base solution). Patients will be assigned randomly in a 1:1:1:1 ratio to hUC–MSC groups and control group, respectively. In stage 3, there are two treatment arms. Patients will be assigned randomly in a 1:1 ratio to the hUC–MSC group and control group, respectively. To avoid ethical problems, we designed an add-on trial. Patients in the placebo-controlled group will receive a placebo while they already receive an established regular treatment (azathioprine or mycophenolate mofetil). Therefore, the allocation ratio of 1:1 was based on optimal statistical power and add-on trial design. In stages 2 and 3, all the participants, investigators, and statistician are blinded to group allocation until the end of the study and data analysis. Only pharmacists who are in charge of preparing study drugs are not blinded. Double-blinding will be performed *via* a centralized randomization system. Subjects who leave the study after random allocation will not be replaced.

### Sample Size Estimation

Based on previous epidemiology studies on NMOSD among Asians, the replacing rate for the patients in the first year of the onset event is estimated at 55% (27). In this study, we expected that the relapsing rate could be reduced to 40% in the MSC group, according to our preliminary data. In the first stage of an exploratory study, each dosage cohort will include 10 patients to meet the safety evaluation goal, which are 30 patients in total. In the adaptive design stages 2 and 3, a total sample size of 400 patients would have 80% power to detect 15% relapsing rate reduction at a two-sided 5% significant level, with a 20% expected loss to follow-up rate. Therefore, we expected to enroll a total number of 430 subjects in this study. The sample size of this study was determined according to the stage of trial by R software (Version 4.0.3).

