**Methods:**

The trial is planned to recruit 430 AQP4-IgG seropositive NMOSD patients. It consists of three consecutive stages. The first stage will be carried out in the leading center only and aims to evaluate the safety of hUC—MSCs. Patients will be treated with three different doses of hUC–MSCs: 1, 2, or 5 × 10^6^ MSC/kg·weight for the low-, medium-, and high-dose group, respectively. The second and third stages will be carried out in six centers. The second stage aims to find the optimal dosage. Patients will be 1:1:1:1 randomized into the low-, medium-, high-dose group and the controlled group. The third stage aims to evaluate the effectiveness. Patients will be 1:1 randomized into the optimal dose and the controlled group. The primary endpoint is the first recurrent time and secondary endpoints are the recurrent times, EDSS scores, MRI lesion numbers, OSIS scores, Hauser walking index, and SF-36 scores. Endpoint events and side effects will be evaluated every 3 months for 2 years.

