The first stage of the trial, which will last 24 months, is an open-labeled study and will be carried out in the leading center only. The first stage aims to evaluate the safety of the infusion of hUC–MSC in NMOSD patients. Patients (*n* = 30) will be treated with three different doses of hUC–MSC. According to the process of enrollment, the first to the tenth participant is in the low-dose group (*n* = 10, 1 × 10^6^ MSC / kg·weight); the eleventh to the twentieth participant is in the medium-dose group (*n* = 10, 2 × 10^6^ MSC / kg·weight); the twenty-first to the thirtieth participant are in the high-dose group (*n* = 10, 5 × 10^6^ MSC / kg·weight). The study starts from the low dose. Only when the lower dose group ends the observation period of 3 months, the study will proceed to a higher dose group. In case of unacceptable toxic reaction occurs in the dose escalation, the study will be ended immediately. In relation to safety considerations, before enrolling the patients in the low-dose group, we will give a single medium dose of hUC–MSC to one patient and follow-up the therapy for one year. The outcome of this dosage will be used only for safety evaluation, not to evaluate the therapy's effectiveness.The second and third stages of the study protocol are part of the multi-center double-blinded randomized clinical trial. The second stage, which aims to screen out the optimal dosage, will last for 24 months and will be carried out in six centers (one leading center and five branch centers). Patients (*n* = 160) will be randomized into four groups: the low-, medium-, high-dose groups, and the controlled group (*n* = 40, respectively). In the second stage, we were seeking to determine the ‘optimal biological dose.’ The dose that allows reaching the optimal efficacy-toxicity trade-off is further selected and recommended to stage 3. The third stage, which aims to evaluate the effectiveness, will last for 24 months and will be developed in six centers. Patients (*n* = 320) will be randomized into two groups: the optimal dose group (*n* = 160) and the controlled group (*n* = 160). The third stage aims to evaluate the effectiveness and safety of hUC–MSC for NMOSD patients. The study flow chart is shown in Figure 1.

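### The stage sizes add to 510, not the stated 430; the figure of 400 cannot be both the stage 2 and 3 enrolment and the number compared, so the 80% power is unsupported as written

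*Protocol article*

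**What the plan says.** Four statements in the protocol article bear on this.

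- **Abstract, Methods:** "The trial is planned to recruit 430 AQP4-IgG seropositive NMOSD patients".
- **Study Design, stage 2:** "Patients (*n* = 160) will be randomized into four groups", 40 in each of three dose groups and control.
- **Study Design, stage 3:** "Patients (*n* = 320) will be randomized into two groups: the optimal dose group (*n* = 160) and the controlled group (*n* = 160"). Stage 1 has 30 patients.
- **Sample Size Estimation:** the control rate comes from a cited epidemiological study, where "the replacing rate for the patients in the first year of the onset event is estimated at 55" per cent, and "we expected that the relapsing rate could be reduced to 40% in the MSC group". Then "a total sample size of 400 patients would have 80% power to detect 15% relapsing rate reduction at a two-sided 5% significant level"; the same sentence allows for one patient in five being lost. With the 30 from stage 1, "we expected to enroll a total number of 430 subjects in this study".

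The Statistical Analysis section combines stages 2 and 3 with an inverse normal test. It analyses time to first recurrence by Kaplan–Meier and Cox methods. Study Design gives every patient 2 years of follow-up.

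**The concern.** The figure of 400 does two jobs. It is the enrolment of stages 2 and 3 (430 less 30), and it is the number said to give 80% power. Stage 2 splits its patients equally over four arms, and two of those arms are not carried into the optimal-dose versus control comparison. The number enrolled in stages 2 and 3 must therefore exceed the number compared by 80, so 400 cannot be both. The stage sizes in Study Design match neither stated total.

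The number of patients to be newly randomised in stage 3 (240 or 320) is therefore not determined by the article. A null result might also be read as coming from a trial with 80% power when the comparison made had less on the stated inputs.

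**Working it through.** **Inputs** (Sample Size Estimation, Study Design): p1 = 0.55, p2 = 0.40, two-sided 5%, 80% power, 20% loss; stage sizes 30, 4 × 40 and 2 × 160.

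**1. Counts.** 30 + 160 + 320 = 510, against 430 stated. 160 + 320 = 480, against 400 stated. Both gaps are 80, which is two stage 2 arms of 40. The totals close if the stage 2 optimal-dose and control patients are counted within the 320: 320 − 80 = 240 new patients, 160 + 240 = 400, and 30 + 400 = 430.

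**2. Reproducing the 400.**

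- *Two proportions, pooled variance:* n per arm = [1.96 √(2 × 0.475 × 0.525) + 0.8416 √(0.55 × 0.45 + 0.40 × 0.60)]² / 0.15² = 172.8, so 173 per arm and 346 in total. 346 / 0.8 = 433; 346 × 1.2 = 416. Neither is 400.
- *Log-rank (Schoenfeld):* HR = ln 0.60 / ln 0.45 = 0.640. Events = 4 (1.96 + 0.8416)² / (ln 0.640)² ≈ 158. Mean one-year event proportion = (0.55 + 0.40) / 2 = 0.475, so 158 / 0.475 = 333 patients. 333 × 1.2 = 400; 333 / 0.8 = 417.

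So 400 is recovered as a log-rank sample size inflated by 1.2, provided that all 400 are in one 1:1 comparison.

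**3. Power for the patients compared, on the stated first-year rates, with the 20% lost removed entirely.**

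Two proportions: power = Φ{[0.15 √n − 1.96 √(2 × 0.475 × 0.525)] / √(0.55 × 0.45 + 0.40 × 0.60)}, with n evaluable per arm. Log-rank: power = Φ{½ √d × |ln HR| − 1.96}, with d events.

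| | 320 includes 80 from stage 2 | 320 are all new |
|---|---|---|
| Enrolled in stages 2 and 3 / in all | 400 / 430 | 480 / 510 |
| Compared, per arm | 40 + 120 = 160 | 40 + 160 = 200 |
| Evaluable per arm (× 0.8) | 128 | 160 |
| Power, two proportions | 67.3% | 76.9% |
| Events (evaluable total × 0.475) | 121.6 | 152 |
| Power, log-rank | 69.3% | 78.6% |
| Power, simulated inverse normal test on proportions | about 68% | about 77% |

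The simulation weights the stages by size, uses a critical value of 1.96, and models no dose selection.

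**4. Two-year follow-up.** The article gives no 2-year rate. If the first-year hazards persisted (an assumption), the 2-year proportions would be 1 − 0.45² = 0.7975 and 1 − 0.60² = 0.64, with mean 0.719. Then 320 × 0.8 × 0.719 = 184 events and 85.8% power; 400 × 0.8 × 0.719 = 230 events and 92.3% power.

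None of these figures includes the cost of choosing among three doses or of the alpha-spending boundary.

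**The case against.** The best defence is that the primary analysis is time to event over 2 years, so a fixed one-year comparison understates the power. This stands in part. If first-year hazards persisted, 320 patients would give about 86%. Censoring patients at dropout, instead of removing them, also helps: under constant dropout (again an assumption), log-rank power at one year is 74.6% for 320 and 83.5% for 400, and at two years about 90% for 320. But the article bases its sample size on a first-year rate and gives no rate for the second year, so these figures are not on its stated inputs.

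A second defence is that the 400 can be reproduced. It can, by the log-rank route with inflation by 1.2, but only for 400 patients in one two-arm comparison. Enrolling 400 in stages 2 and 3, with a quarter of stage 2 in each arm, cannot supply that.

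Three stronger readings are tempting and are not supported:

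- *The trial both totals 510 and has 67% power.* These belong to opposite readings. A comparison of 320 requires the carry-forward that makes 430 correct. A total of 510 gives 400 compared and about 77% to 79%.
- *No reading of the sizes gives 80%.* With 400 compared, log-rank power is 78.6%, and the stated 400 is recovered with the 1.2 inflation.
- *The centres or the randomisation system do not know the stage 3 target.* The article condenses a fuller protocol that is not shown and may settle it. What can be said is that the article prints both sets of figures and they conflict.

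**Conclusion.** Wrong as written. The contradiction between 510 and 430 (480 and 400 for stages 2 and 3) rests on addition alone. Its effect on power depends on which reading is meant, and the article does not settle that: the wording of stage 3, in which 320 are to be randomised, points to all-new patients, while the totals point to 80 carried forward.

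- If carried forward, the totals stand and the power statement fails: about 67% to 69%, a shortfall of 11 to 13 points.
- If all new, the power statement is nearly right, at about 77% to 79%, and the totals of 400 and 430 are each 80 too low.

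These figures assume the stated first-year rates, a two-sided 5% test, and 20% of patients contributing nothing. A reader might conclude that the trial's true power is 67%. That does not follow, because the figure depends on one reading and on a one-year horizon that is shorter than the planned follow-up.

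**What to change.** 1. State in Study Design whether the 320 of stage 3 includes the stage 2 patients on the selected dose and control, and give the number newly randomised in stage 3 (240 or 320).
2. Make the Abstract, Study Design and Sample Size Estimation agree: either 400 for stages 2 and 3 and 430 in all, or 480 and 510.
3. Replace the 80% statement with the power for the patients in the optimal-dose versus control comparison (320 or 400). Compute it for the planned time-to-event inverse normal combination test, with an explicit event rate over the 2-year follow-up, a stated treatment of loss, and the cost of dose selection. Neither 67% nor 86% should simply be written in: the first uses only the first-year rates, and the second rests on an unstated hazard assumption and omits dose selection.

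This takes wording changes and one recalculation, with no extra patients. The downside is that either the stated power or the stated total may become less favourable.
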